## Abstract

**Introduction:**

In current practice, probands are asked to inform relatives about the possibility of predictive DNA testing when a pathogenic variant causing an inherited cardiac condition (ICC) is identified. Previous research on the uptake of genetic counselling and predictive DNA testing in relatives suggests that not all relatives are sufficiently informed. We developed a randomised controlled trial to evaluate the effectiveness of a tailored approach in which probands decide together with the genetic counsellor which relatives they inform themselves and which relatives they prefer to have informed by the genetic counsellor. Here, we present the study protocol of this randomised controlled trial.

**Methods:**

A multicentre randomised controlled trial with parallel-group design will be conducted in which an intervention group receiving the tailored approach will be compared with a control group receiving usual care. Adult probands diagnosed with an ICC in whom a likely pathogenic or pathogenic variant is identified will be randomly assigned to the intervention or control group (total sample: n=85 probands). Primary outcomes are uptake of genetic counselling and predictive DNA testing by relatives (total sample: n=340 relatives). Secondary outcomes are appreciation of the approach used and impact on familial and psychological functioning, which will be assessed using questionnaires. Relatives who attend genetic counselling will be asked to fill out a questionnaire as well.

**Ethics and dissemination:**

Ethical approval was obtained from the Medical Ethical Committee of the Amsterdam University Medical Centres (MEC 2017-145), the Netherlands. All participants will provide informed consent prior to participation in the study. Results of the study on primary and secondary outcome measures will be published in peer-reviewed journals.

**Trial registration number:**

NTR6657; Pre-results.

Strengths and limitations of this studyThis randomised controlled trial investigates both the uptake of genetic counselling and of predictive DNA testing, as well as the acceptance and impact on psychological and family functioning in the tailored versus the standard approach, in probands and relatives.This study will be conducted in three clinical genetics clinics with expertise on cardiogenetics, which will facilitate participant inclusion.In this trial, evaluation of the effect on outcome of the different components of the intervention is not possible, due to limited power.In this randomised controlled trial it is not possible to blind participants, genetic counsellors or the executing investigator for the chosen intervention.Because a baseline measure for the secondary outcomes is not possible, we cannot control for likely confounding factors such as intention to inform at-risk relatives, and family and psychological functioning at baseline.

## Introduction

Inherited cardiac conditions (ICCs) such as cardiomyopathies and primary arrhythmia syndromes generally demonstrate an autosomal dominant inheritance pattern and a wide variety of symptoms that can manifest at any age.^1 2^ One feared outcome is sudden cardiac death (SCD), which can occur at a young age and be the first symptom of disease.^3 4^ With an incomplete penetrance and high variability in expression even within families, carriers of a familial variant may remain undetected but still be at risk for SCD even though treatment options are available that prevent disease progression or potentially life-threatening arrhythmias.^5^ Predictive DNA testing is therefore offered to first-degree relatives of probands (the first person in a family diagnosed with an ICC) in whom a pathogenic variant is identified because these relatives are at 50% risk of also having inheriting the genetic variant.^5 6^ Predictive DNA testing is offered to relatives in a stepwise manner (cascade screening), with the aim of identifying asymptomatic carriers of the familial variant to facilitate timely treatment. Non-carriers of the familial variant generally do not need cardiac monitoring and can be reassured about their own risk and that of their offspring.^6^

In current practice in the Netherlands, probands are asked to inform their relatives, supported by a family letter written by the genetic counsellor. This is referred to as the family mediated approach.^7^ Previous research, however, shows that uptake (the number of relatives at risk attending genetic counselling and/or undergoing predictive DNA testing) is relatively low in ICCs, particularly for cardiomyopathies. Reported uptakes are around 50% despite family letters being provided to a majority of relatives by the proband.^8–10^ Previous research in other genetic patient populations, such as hereditary types of cancer, shows similar uptake percentages.^11–13^

Some relatives who do not attend genetic counselling will have deliberately decided against predictive DNA testing. However, the low uptake percentages also suggest that many relatives may be unaware, or insufficiently aware, of the risks involved and/or the possibilities for genetic counselling and subsequent surveillance and treatment. This is supported by research on family communication in ICCs. Patients are not always able to inform or correctly inform their relatives for a number of reasons, including disengagement with relatives, lack of understanding of the importance of the information, preoccupation with their own grief, difficulties in conveying the complex information to relatives or a wish to prevent burdening relatives by informing them about genetic risks.^8 14–18^

Previous studies assessing interventions to enhance family communication in hereditary diseases showed that some interventions are effective in increasing the uptake of genetic counselling.^19–21^ An intervention trial aimed at improving family communication in specifically dilated cardiomyopathy is still ongoing.^22^ A few studies have been published on more active approaches to informing relatives at risk in which healthcare professionals (HCPs) contact at-risk relatives directly.^23–26^ These studies suggest that a more active approach can almost double the uptake of genetic counselling and predictive DNA testing by relatives. However, some of these studies were performed in a research setting (eg, in relatives already registered in research databases for the genetic disease), hampering direct translation of these results to a diagnostic setting. To our knowledge, more active approaches in patients with ICCs have not been studied thus far. However, a study by Ormondroyd *et al*
14 suggests that relatives eligible for predictive DNA testing for hypertrophic cardiomyopathy and long QT syndrome would support a more active approach to informing relatives at risk.

Although studies on more active approaches did not report any psychological harm in relatives at group level, these approaches could cause more unwarranted worry or pressure on relatives to opt for predictive DNA testing.^23–25^ An active approach to informing relatives at risk could also breach the autonomy and confidentiality of probands, and may harm relative’s right not to know.^27–29^ Furthermore, HCPs are often unaware of interpersonal dynamics within families and the personal circumstances of relatives at risk. Active approaches may therefore have a negative impact on family relationships or may cause psychological distress in both probands and relatives.^30^

Because of this, a tailored approach in which a proband decides together with the genetic counsellor which at-risk relatives he or she will inform and which relatives he or she prefers to be informed by the genetic counsellor could be optimal. With this approach, the probands expert knowledge of a relative’s functioning and of family dynamics could be used appropriately, and the autonomy of the proband preserved. At the same time, more relatives at risk would be sufficiently informed.^28 30^ Furthermore, probands for whom informing relatives is difficult or burdensome might be relieved or supported by this approach.^30^

### Objectives

The primary aim of this randomised controlled trial is to assess whether uptake of genetic counselling and testing of relatives at risk of an ICC will be increased by using a tailored approach to information provision for relatives, instead of usual care (ie, the family-mediated approach). Secondary objectives are to evaluate how such a tailored approach is appreciated by both probands and relatives as compared with usual care. In addition, this study aims to assess the perceived impact on family relationships and psychological functioning of both probands and relatives. The protocol presented here has been described based on the ’Standard Protocol Items: Recommendations for Interventional Trials (SPIRIT) statement.^31^

## Methods

### Design

A multicentre randomised controlled trial with a parallel-group design will be conducted in three university hospitals in the Netherlands (the Amsterdam University Medical Centres (Amsterdam UMC), the University Medical Centre Utrecht (UMCU) and the University Medical Centre Groningen (UMCG)) to compare the effects of a tailored approach to informing relatives at risk of ICCs to usual care in both probands and relatives.

### Participants

All probands aged 18 years or older with an ICC, or suspicion thereof, attending pre-test genetic counselling at the cardiogenetics outpatient clinics during the inclusion period will be asked to participate if they: (1) are the first member of their family to visit the cardiogenetics outpatient clinic for counselling about genetic testing for ICCs; (2) have at least one living adult relative; and (3) are able to read and write Dutch. Only probands in whom a likely pathogenic or pathogenic variant is detected (class 4—likely pathogenic or class 5—pathogenic variant) will be definitively included.

In addition, eligible adult first/second-degree relatives of enrolled probands who make an appointment at the cardiogenetics outpatient clinics will be invited to fill out a questionnaire to measure secondary outcomes. Inclusion criteria are defined as follows: (1) first-degree adult (18 years or older) relatives of probands enrolled in the study or second-degree adult relatives in case of a deceased connecting first-degree relative who was affected or suspected to be affected, and (2) able to read and write Dutch.

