#### Recruitment and consent

During pre-test genetic counselling, the genetic counsellor will inform the probands about the study and provide an informational letter (see online supplementary material S1). In addition, probands will be asked if the executing researcher can contact them to provide further information about the study. Subsequently, probands will be contacted by telephone by the executing researcher. If probands are still interested in participation, written informed consent forms will be sent by post, including a return envelope. As described earlier, only probands in whom a likely pathogenic or pathogenic variant is detected will be definitively included in the study.

10.1136/bmjopen-2018-025660.supp1Supplementary data

Relatives of enrolled probands attending pre-test genetic counselling in one of the participating centres who are also at risk will also be invited to participate in the study. The same recruitment procedure will be used.

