#### Measurement time points

For secondary outcome measures, participating probands will be asked to complete a questionnaire 1 month after receiving the genetic test result (T1) and to complete a second questionnaire 9 months after the test result (T2). Before T1 and T2, a short structured telephone interview will be conducted about participant’s knowledge of which relatives are at risk of ICCs and which relatives are informed, because these items are expected to be too complex to answer in a questionnaire.^33^ Participating relatives will complete one questionnaire after attending genetic counselling.

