### Data analysis

#### Statistical analysis

Sociodemographic, clinical, psychosocial and personality variables will be analysed using descriptive and frequency statistics. An intention-to-treat approach will be used. SPSS V24.0 will be used to perform statistical analyses.^44^ An α level of p<0.05 will be used. Analysis of variance and χ tests will be used to assess differences (1) in sociodemographic, clinical and psychological characteristics between the intervention and control groups and (2) in participants and non-participants, as appropriate. Descriptive and frequency statistics will be used to describe the primary outcomes: (1) uptake of genetic counselling and (2) uptake of predictive DNA testing. Logistic regression analysis will be conducted to assess differences between the intervention and control groups on the primary outcomes, with the randomisation group as the main exploratory variable. Two logistic regression models will be used, with the first model including only the randomisation group and the second model also including the potential covariates (ie, sociodemographic, clinical and psychological variables). Multilevel analyses will be performed to assess whether the randomisation group, that is, the independent variable, has an impact on family and psychological functioning, that is, the secondary outcome variables. The two measurement time points in probands will be treated as nested within probands. To prevent influence of potential confounding factors, multilevel analysis will be adjusted for covariates as well. Participant appreciation of the approach used will be described using frequency statistics.

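### Family and psychological impact in relatives is measured only in those who come for counselling, so the comparison between arms is conditional on a primary outcome and is not a randomised one.

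*Protocol article*

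**What the plan says.** Four places in the protocol article agree on who among the relatives is measured.

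- Abstract, Methods: "Relatives who attend genetic counselling will be asked to fill out a questionnaire as well".
- Participants: "eligible adult first/second-degree relatives of enrolled probands who make an appointment at the cardiogenetics outpatient clinics will be invited to fill out a questionnaire".
- Recruitment and consent: "Relatives of enrolled probands attending pre-test genetic counselling in one of the participating centres who are also at risk will also be invited".
- Measurement time points: "Participating relatives will complete one questionnaire after attending genetic counselling".

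Primary outcome measures makes relatives' uptake of counselling a primary outcome, and Sample size calculation expects 50% under usual care and 65% under the tailored approach.

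The Objectives say that "this study aims to assess the perceived impact on family relationships and psychological functioning of both probands and relatives". Design describes a comparison of the two approaches in probands and relatives alike, and the strengths and limitations box lists this among the strengths. Secondary outcome measures gives the adapted ODCF, adapted CWS and HADS to both groups.

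Under Statistical analysis, "Multilevel analyses will be performed to assess whether the randomisation group, that is, the independent variable, has an impact" on family and psychological functioning. That section also states an intention-to-treat approach in general terms. It names neither a separate model for relatives nor a restriction to probands. Appreciation is to be described with frequencies only.

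**The concern.** The relatives' scores exist only for people selected by an event that happens after randomisation and that the intervention is designed to change. If the tailored approach works, its attenders include people who would have stayed away under usual care. The two groups of attenders can then differ in worry, anxiety or family openness for reasons unrelated to any effect on those outcomes. A group coefficient from this sample, reported under the intention-to-treat label, would look like a randomised estimate without being one.

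The second issue is what the sample cannot contain. The Introduction warns that "these approaches could cause more unwarranted worry or pressure on relatives to opt for predictive DNA testing" and raises the right not to know. In the intervention arm the counsellor's letter goes to every at-risk relative for whom the proband agrees to contact, whether or not that relative later attends. A relative upset by the letter who stays away contributes no score. A report of no psychological difference in relatives would say nothing about that person.

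**Working it through.** **Inputs from the protocol.** Uptake 50% and 65%, two-sided 5% level, 80% power, 170 relatives per arm, four eligible adult relatives per proband (Sample size calculation); 1:1 allocation (Randomisation).

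**1. The plan's own figure.** For two proportions with pooled variance under the null, n = [1.96·√(2·0.575·0.425) + 0.842·√(0.50·0.50 + 0.65·0.35)]² / 0.15² = 169.3, so 170 per arm and 340 in all. 340/4 = 85 probands. The stated sample size reproduces, and this point does not depend on any error in it.

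**2. Relatives who can be observed at planned uptake.**

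| | Control | Intervention |
|---|---|---|
| Relatives | 170 | 170 |
| Attend | 0.50 × 170 = 85 | 0.65 × 170 = 110.5 |
| Never measured | 85 | 59.5 |

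Never measured in total: (85 + 59.5)/340 = 42.5%. The attender counts are upper limits, because relatives counselled outside the participating centres are not recruited and some of those invited will not respond.

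**3. Attenders without a counterpart.** If the intervention deters no one, the share of intervention attenders who come only because of it is 1 − 0.50/0.65 = 23%.

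**4. Selection bias with no true effect.** The documents give no correlation between worry and attending, so a range is assumed. Under a normal model with attendance probability p and correlation r, mean worry among attenders is r·φ(c)/p, where c is the normal cut-off for p.

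- p = 0.50: φ(c)/p = 0.798
- p = 0.65: φ(c)/p = 0.570
- Intervention minus control = −0.228·r

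| r | Arm difference (SD) |
|---|---|
| 0.2 | −0.046 |
| 0.3 | −0.068 |
| 0.5 | −0.114 |

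A negative r of the same size reverses the sign. As a second route, let the extra attenders differ from the others by an assumed 0.3 to 0.8 SD. The spurious difference is then 0.23 × 0.3 to 0.23 × 0.8, that is 0.07 to 0.18 SD, again in either direction.

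**5. Bias set against precision.** With 85 and 110.5 attenders, the standard error of the arm difference is √(1/85 + 1/110.5) = 0.144 SD, ignoring clustering in families and non-response. The bias in step 4's table is 0.3 to 0.8 standard errors. A 5% test with no true effect would reject about 6%, 8% and 12% of the time at r = 0.2, 0.3 and 0.5.

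**6. Harm that cannot be seen.** Assume harm of 0.2 to 0.8 SD confined to intervention relatives who do not attend (35%). Averaged over all intervention relatives this is 0.35 × 0.2 to 0.35 × 0.8, that is 0.07 to 0.28 SD. The comparison among attenders would show zero.

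**7. Whether the planned adjustment helps.** Relatives' psychosocial covariates come from the same questionnaire respondents, so adjusting for them cannot recover the relatives who were never asked.

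**The case against.** The strongest reply has four parts.

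*The test in relatives is inferred.* The multilevel sentence does not name relatives, and the only nesting it describes is two time points within probands. An analysis plan not shown here may label the relatives' model as conditional on attendance. This stands as a caution. Still, the objectives, the design statement, the listed strengths and the instruments all treat relatives as part of the comparison, and the article gives no other analysis of their impact scores.

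*The bias is small.* This also stands. It rests on assumed correlations, its sign is open, and it is below one standard error. The difference detectable with 80% power is about 2.80 × 0.144 = 0.40 SD, so imprecision limits a no-harm claim more than this bias does. Harm outside the sample is a separate matter that this argument does not reach.

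*Probands give partial cover.* They are measured at T1 and T2 without selection on relatives' attendance and report changes in family relationships. That captures some family-level harm, but not a non-attender's own distress.

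*The restriction is openly stated.* It is, and the article itself draws no conclusion of no harm. The listed limitations mention the missing baseline but not this selection.

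A reader might also infer two stronger things that the documents do not support. One is that the feared harm falls mainly on contacted relatives who stay away. The Introduction also names pressure to be tested, and a relative pressed into testing would be an attender, so only part of the concern is out of sight. The other is that appreciation is tested in the same way. It is planned as descriptive and lies outside this point.

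**Conclusion.** The point holds for relatives' ODCF, CWS and HADS. As written, the plan invites a comparison selected on a primary outcome to be read as a randomised effect on relatives. At the planned uptake, about 145 of 340 relatives are unobserved by design, and about 23% of intervention attenders lack a control counterpart if nobody is deterred. The bias among attenders is modest under the assumed correlations and could go either way, so the documents do not support calling the comparison badly distorted. What they do support is that it is not protected by randomisation and cannot speak for contacted relatives who stay away. The primary outcomes and the proband comparison are not affected by this selection.

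**What to change.** - Base randomised inference on psychological and family impact on probands at T1 and T2.
- Restate the relatives' objective as applying among relatives who attend counselling.
- Report relatives' ODCF, CWS and HADS by arm as conditional on attendance and outside the intention-to-treat analysis, with attendance and questionnaire response by arm alongside.
- Draw no causal conclusion, and no conclusion of no harm in relatives, from that comparison.
- Add this selection to the stated limitations.

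This needs no new data and no change to the sample size. The cost is a narrower claim about relatives. It does not close the gap for non-attenders, whose distress remains unmeasured. Surveying them would be difficult: the article describes collecting relatives' contact details only in the intervention arm and with the proband's consent, and further contact could itself conflict with the right not to know.

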### Procedure

Figure 1 shows a flowchart of the study procedure.

**Figure 1 F1:**
[figure not shown]
Flowchart of the study procedure.

#### Recruitment and consent

During pre-test genetic counselling, the genetic counsellor will inform the probands about the study and provide an informational letter (see online supplementary material S1). In addition, probands will be asked if the executing researcher can contact them to provide further information about the study. Subsequently, probands will be contacted by telephone by the executing researcher. If probands are still interested in participation, written informed consent forms will be sent by post, including a return envelope. As described earlier, only probands in whom a likely pathogenic or pathogenic variant is detected will be definitively included in the study.

10.1136/bmjopen-2018-025660.supp1Supplementary data

Relatives of enrolled probands attending pre-test genetic counselling in one of the participating centres who are also at risk will also be invited to participate in the study. The same recruitment procedure will be used.

